## Abstract

**Background::**

Ventriculoperitoneal shunt (VPS) and lumboperitoneal shunt (LPS) remain the mainstay of idiopathic normal pressure hydrocephalus (INPH). There are no randomized controlled trials completed to compare the efficacy of these 2 shunt techniques.

**Methods/design::**

We will conduct a monocentric, assessor-blinded, and randomized controlled trial titled “Comparison of Ventriculoperitoneal Shunt to Lumboperitoneal Shunt for the treatment of Idiopathic Normal Pressure Hydrocephalus: Phase I (COVLINPH-1)” trial and recruit patients at West China Hospital of Sichuan University since June 2021. And this trial is expected to end in December 2030. Eligible participants will be randomly assigned into LPS group and VPS group at ratio of 1:1 followed by evaluation before surgery, 1 month, 12 months, and 5 years after surgery. The primary outcome is the rate of shunt failure within 5 years. The secondary outcomes include modified Rankin Scale (mRS), INPH grading scale (INPHGS), mini-mental state examination (MMSE), and Evans index. We will calculate the rate of favorable outcome, which is defined as shunt success and an improvement of more than 1 point in the mRS at evaluation point. We will also analyze the complications throughout the study within 5 years after shunt insertion.

**Discussion::**

The results of this trial will provide state-of-the-art evidence on the treatment option for patients with INPH, and will also generate the discussion regarding this subject.

**Trial registration number::**

ChiCTR2000031555; Pre-results.

## Introduction

1

Idiopathic normal pressure hydrocephalus (INPH) is a common geriatric disorder that has unknown causes featured as the triad of Hakim-Adams syndrome (gait/balance disturbance, dementia, and urinary incontinence), accompanying with ventriculomegaly but normal intracranial pressure.^[1,2]^ Early evidence indicated around 1.5% of elderly (>60 years) per year was estimated to develop INPH.^[3,4]^ Although the pathophysiological mechanisms of INPH have not been fully understood, there is a few evidences showing increased arterial pulse pressure might involve in the development of INPH.^[5,6]^

Currently, cerebrospinal fluid (CSF) shunts including ventriculoperitoneal shunt (VPS) and lumboperitoneal shunt (LPS) remain the mainstay of INPH.^[7]^ VPS is the most commonly used and widely studied treatment and LPS is an important and alternative option. Bur growing number of studies recently suggest LPS is the preferred and superior option since several advantages, particularly the avoidance of brain injury. In this regard, LPS has become the first-line and most commonly used methods to treat INPH in Japan.^[8,9]^

Over the past few decades, a great deal of attention has been given with the respect to the best treatment for INPH. There are some studies suggesting no significant differences among the different shunts used, which are mainly retrospective design.^[10]^ Miyajima et al^[11]^ conducted a prospective and multi-center trial on the efficacy and safety of LPS for the treatment of INPH, indicating the incidence of shunt revisions of LPS (7%) is slightly higher compared with a historical trial that test the efficacy of VPS for the treatment of INPH (1%), and despite the risk of shunt failure, LPS could be the superior option considering about the minimally invasiveness. To date, there are no randomized controlled trials completed to compare the efficacy of these 2 shunt techniques, therefore, it is difficult to draw strong conclusions regarding the optimal treatment.^[12]^

## Objective

2

The objective of this trial is to compare the efficacy and safety of VPS to LPS for the treatment of patients with INPH.

## Methods and design

3

### Ethic and dissemination

3.1

This trial will follow the Guidelines for Good Clinical Practice and the Declaration of Helsinki (2002) of the World Medical Association, and implement the principles and requirements of informed consent, privacy protection, research free and compensation, risk control, protection of special subjects and compensation for research related damages. Before the start, the Institutional Review Board of West China Hospital has approved the study on February 20, 2020. The study has registered through Chinese Clinical Trial Registry in April 2020 (ChiCTR2000031555).

Before recruitment, the researcher has the responsibility to completely and comprehensively introduce the purpose, procedure and possible risks of this study to the subject or / and his legal representative, and sign a written informed consent. The subjects should be fully informed that they are completely voluntary to participate in the clinical study, and they can refuse to participate in or withdraw from this study at any stage of the trial. When it comes to discrimination and revenge, their medical treatment and rights will not be affected. Informed consent should be kept as clinical research documents for future reference to protect the privacy and data confidentiality of subjects.

We will share the data on ResMan Research Manager within 6 months after the trial complete and the results will be published in peer-reviewed journals, together with conferences.

### Study design

3.2

We will conduct a monocentric, assessor-blinded, and randomized controlled trial titled “Comparison of Ventriculoperitoneal Shunt to Lumboperitoneal Shunt for the treatment of Idiopathic Normal Pressure Hydrocephalus: Phase I (COVLINPH-1)” trial and recruit patients at West China Hospital of Sichuan University since June 2021. And this trial is expected to end in December 2030. Eligible participants will be randomly assigned into LPS group and VPS group at ratio of 1:1 followed by evaluation before surgery, 1 month, 12 months, and 5 years after surgery. The primary outcome is the rate of shunt failure within 5 years. The secondary outcomes include modified Rankin Scale (mRS), INPH grading scale (INPHGS), mini-mental state examination (MMSE), and Evans index. We will calculate the rate of favorable outcome, which is defined as shunt success and an improvement of more than 1 point in the mRS at evaluation point. We will also analyze the complications throughout the study within 5 years after shunt insertion.

### Recruitment and eligibility

3.3

The flow chart of the selection of patients is shown in Fig. 2. Once the eligible participants are admitted, 3-dimension brain and spine magnetic resonance imaging scan will be first performed to further evaluate the ventricles, aqueduct, basal cisterns, and spinal subarachnoid space before shunt surgery. Each participant will receive financial compensation. The inclusion and exclusion criteria are shown as follows:

### Inclusion criteria

3.4

1.Age >40 years;2.Idiopathic or insidious onset;3.At least 2 following symptoms: gait/balance disturbance, impairment in cognition, urinary incontinence.4.Evans index >0.3;5.The CSF opening pressure is 70 to 200 mmH_2_O.

### Exclusion criteria

3.5

1.Secondary hydrocephalus;2.Obstructive hydrocephalus;3.Chiari malformation;4.Parkinson's disease;5.Alzheimer's disease.

### Sample size

3.6

A recent meta-analysis systematically reviewed the shunting outcomes in patients with INPH and showed the rate of VPS failure and LPS failure were 18.0% and 14.0%, respectively.^[13]^ Therefore, a sample of 250 for each group will be required in this trial with a significance level of 5% (two-sided) and a power of 80% to demonstrate a 20% difference. Finally, the sample size will be enlarged to 300 for each group.

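### The planned 250 per group, 80% power and 20% target do not fit the quoted failure rates of 18% and 14%: power for those rates is about 23% (27% with 300 per group)

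*Protocol article*

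**What the plan says.** The Sample size section (3.6) cites a meta-analysis in which "the rate of VPS failure and LPS failure were 18.0% and 14.0%, respectively". It presents the sample size as a consequence of those rates: 250 per group are said to be needed "with a significance level of 5% (two-sided) and a power of 80% to demonstrate a 20% difference". It then enlarges each group to 300 without giving a reason. It does not say whether the 20% is absolute or relative.

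Elsewhere the article fixes the rest of the calculation. Allocation is 1:1 (3.2), the primary outcome is the proportion with shunt failure within 5 years (3.12), and categorical variables are compared by the chi-squared test (3.15).

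**The concern.** The two quoted rates differ by 4 percentage points, or 4/18 = 22% in relative terms. A 4-point difference between proportions near 16% cannot be detected with 80% power by 250 per group. A 20-point difference is five times the quoted gap and would need far fewer than 250. The target therefore matches the quoted rates only loosely, as a relative difference, and on that reading the sample size is far too small.

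The stated power is what a reader uses to interpret the primary result. If the failure rates are close to those the protocol quotes, the primary test will miss the difference about three times in four, while the protocol tells the reader it would miss it one time in five.

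**Working it through.** **Inputs, all from the article.** Two-sided alpha 0.05 and power 80% (3.6); failure 18% VPS and 14% LPS (3.6); 250 per group, then 300 (3.6); 1:1 allocation (3.2); binary primary outcome (3.12); chi-squared test (3.15).

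**Formula.** For two proportions with pooled variance under the null, p̄ = (p1 + p2)/2:

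n per group = [1.960·√(2p̄(1−p̄)) + 0.8416·√(p1(1−p1) + p2(1−p2))]² / (p1−p2)²

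**Step 1: try to reproduce 250 from the quoted rates.** With p1 = 0.18, p2 = 0.14, p̄ = 0.16:
- 1.960·√(2·0.16·0.84) = 1.0162
- 0.8416·√(0.1476 + 0.1204) = 0.8416·√0.268 = 0.4357
- n = (1.0162 + 0.4357)² / 0.04² = 2.108 / 0.0016 = 1,317.4, so 1,318 per group

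Other methods do not help: 1,367 with continuity correction, 1,315 with unpooled variance, 1,314 by arcsine, about 1,303 to 1,322 by log-rank formulas, and 1,038 even if the test were one-sided. The stated 250 is not reproduced.

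**Step 2: power at the planned size for 18% against 14%.**

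Power = Φ{[0.04 − 1.960·√(2·0.16·0.84/n)] / √(0.268/n)}
- n = 250: (0.04 − 1.960·0.03279)/0.03274 = −0.741, power 22.9%
- n = 300: (0.04 − 1.960·0.02993)/0.02989 = −0.625, power 26.6%

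Simulating the chi-squared test gives 23.1% and 26.7%.

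**Step 3: other readings of the 20% target, two-sided 5%.**

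| Reading | Rates | n per group for 80% | Power at 250 |
|---|---|---|---|
| Relative, failure | 18% vs 14.4% | 1,644 | 19% |
| Relative, failure | 18% vs 21.6% | 1,923 | 17% |
| Relative, failure | 14% vs 11.2% | 2,204 | 15% |
| Relative, failure | 14% vs 16.8% | 2,608 | 14% |
| Absolute, 20 points | 18% vs 38% | 78 | >99% |
| Absolute, 20 points | 14% vs 34% | 71 | >99% |
| Relative, success | 82% vs 65.6% | 112 | 99% |
| Relative, success | 86% vs 68.8% | 92 | >99% |

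Required sizes fall either near 50 to 125 (the lower end is a relative gain in success, 82% vs 98.4%, at 51) or above 1,600. None is near 250.

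**Step 4: what 250 and 300 per group deliver at 80% power, with one arm at 18%.**
- 250 per group: the other arm at about 9.4% or lower (8.6 points below), or 28.6% or higher (10.6 points above)
- 300 per group: about 10.1% or lower (7.9 points below), or 27.6% or higher (9.6 points above)

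The smallest of these gaps is about twice the quoted 4 points.

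**Step 5: expected precision at 18% and 14%.** The 95% CI half-width for the difference is 1.960·√(0.268/n): 6.4 points with 250 and 5.9 points with 300. Both exceed the 4-point difference.

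**The case against.** The strongest objection is that the section names its target as a 20% difference and does not say that 4 points is the effect to be detected. If 20 percentage points was meant, 250 per group is ample and there is no shortfall. This stands as a limit on the claim: the shortfall applies to the quoted rates and to a relative 20%, not to every reading. It does not rescue the section, because 250 would then exceed the requirement about threefold, the 80% would still be wrong, and a 20-point gap would have no basis in the rates from which the number is said to follow.

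It is also true that some inputs give about 250: a 20% relative reduction from a base rate near 62% needs 251, and a standardised difference of 0.25 needs 252. The article gives neither input, so the statement is confined to readings based on the quoted rates.

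A full protocol or analysis plan might explain more. But this is a contradiction among stated figures, and no further document can make 250 give 80% power for 18% against 14%.

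Three stronger inferences are tempting, and the article does not support them:
- **Conflicting direction.** A reader might set the Introduction, "indicating the incidence of shunt revisions of LPS (7%) is slightly higher compared with a historical trial", against the lower LPS failure rate in 3.6. The Introduction compares revision rates from separate trials (7% and 1%), whereas 3.6 uses pooled failure rates from a meta-analysis, and the trial's own failure definition covers more than revision. The test is two-sided, so no hypothesised direction is needed.
- **A stated loss allowance.** 250/300 = 83.3% would imply 16.7% loss, but 250 × 1.20 is also 300, and the article gives no reason for the enlargement.
- **A planned equivalence claim.** The Objective is only to compare efficacy and safety. How a non-significant result is reported can be left to the analysis plan.

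**Conclusion.** The point holds: the sample size, power, target difference and quoted rates in section 3.6 are mutually inconsistent. If the quoted 18% and 14% are the planning rates, as the section's wording implies, power is about 23% with 250 evaluable per group and 27% with 300, against a stated 80%, and about 1,318 per group would be needed. If 20% is a relative difference in failure, power at 250 is 14 to 19%. If it is 20 points, power is over 99%.

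The result assumes a two-sided 5% comparison of two proportions with 1:1 allocation, as the article describes, and is insensitive to the choice of formula. Which power applies in the end depends on whether the extra 50 per group are lost to follow-up (near 23%) or contribute outcomes (up to 27%).

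**What to change.** Amend section 3.6 as follows, keeping 300 per group:
- Delete the words "to demonstrate a 20% difference" and the 80% power attached to them.
- State that for 18% against 14% power is about 23% with 250 evaluable per group and 27% with 300.
- State that, with one arm at 18%, 80% power is reached only if the other arm is about 9.4% or lower, or 28.6% or higher, with 250 per group (about 10.1% or 27.6% with 300). Both directions are needed because the detectable gap differs above and below 18%.
- Give the expected 95% CI half-width for the difference: about 6.4 points (250) or 5.9 points (300).
- Say whether the extra 50 per group are an allowance for loss to follow-up.

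The cost is a rewording by amendment, with no extra patients and no change in conduct. The downside is that the stated power becomes much less favourable. The change corrects the statement and does not raise the power; detecting 18% against 14% with 80% power would still need about 1,318 per group.

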### Randomizing and blinding

3.7

This trial is randomized and open-label. We will complete the randomization through a random number table, but the data collectors, accessors, and analysts are blinded to allocation.

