### Ventriculoperitoneal shunt

3.9

VPS will be performed under general anesthesia and the proximal shunt tubing will be inserted into the right lateral ventricles. A ventricular catheter is inserted into the lateral ventricle. The valve will be placed at the cranial incision with a 3-point fixation to the subcutaneous tissue. A subcutaneous tunneler is made to connect the valve with abdominal cavity. The peritoneal catheter will be inserted if the CSF flow through shunt catheter is observed.

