### Lumboperitoneal shun

3.10

The patients in the left lateral position under general anesthesia. A lumbar catheter is inserted through the L3/4 interlaminar space into the spinal subarachnoid space. A subcutaneous flank region is then made to fix the valve. A subcutaneous tunneler is made to connect the spinal subarachnoid space, frank region, and abdominal cavity. The peritoneal catheter will be inserted if the CSF flow through shunt catheter is observed.

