**Figure 1 F1:**
[figure not shown]
The schedule of enrolment, interventions, and assessments. # The position of MRI scan include brain, lumbar, and abdomen. ∗ “Shunt outcome” includes shunt failure and shunt success. INPHGS = idiopathic normal pressure hydrocephalus grading scale, LPS = lumboperitoneal shunt, MMSE = Mini-Mental State Examination, MRI = magnetic resonance imaging, mRS = modified Rankin Scale, VPS = ventriculoperitoneal shunt.

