### Data collection and management

3.14

Two independent data collectors will collect the baseline information (age, sex, comorbidities, recruitment time, CSF opening pressure, clinical manifestations, radiological features) at the time of admission, perioperative conditions, and follow-up outcomes at each evaluation point (shunting outcomes, mRS, INPHGS, MMSE, Evans index, complications, serious adverse events). The data is first recorded in paper and then stored in Excel.

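### Blinding is claimed for data collectors whose listed tasks reveal the arm, and shunt failure and Evans index cannot be blinded as described

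*Protocol article*

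**What the plan says.** The Study design section (3.2) opens with "We will conduct a monocentric, assessor-blinded, and randomized controlled trial". Randomizing and blinding (3.7) states "This trial is randomized and open-label" and adds that "the data collectors, accessors, and analysts are blinded to allocation".

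Data collection and management (3.14) sets out the collectors' work: "Two independent data collectors will collect the baseline information" at admission, and then "perioperative conditions, and follow-up outcomes at each evaluation point (shunting outcomes, mRS, INPHGS, MMSE, Evans index, complications, serious adverse events". The Outcomes section (3.11) separately has each participant evaluated at every visit by two independent assessors.

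The two operations leave hardware in different places. For VPS (3.9) a catheter lies in the lateral ventricle, and "The valve will be placed at the cranial incision with a 3-point fixation to the subcutaneous tissue". For LPS (3.10) a catheter enters the spinal subarachnoid space at L3/4, and "A subcutaneous flank region is then made to fix the valve". Primary outcome (3.12) defines shunt failure by a list of hardware faults, infection, and any condition that calls for revision. Secondary outcomes (3.13) takes Evans index from MRI, and the Figure 1 footnote says of the imaging: "The position of MRI scan include brain, lumbar, and abdomen".

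**The concern.** Blinding of the people who record or judge outcomes is the article's stated safeguard against assessment bias in a trial where patients and surgeons know the allocation. If the tasks given to those people reveal the arm, the safeguard is not available where the article says it is. A reader of the final report would then credit the primary outcome and Evans index with a protection that the design cannot deliver.

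The same loose claim also puts at risk the protection that is achievable. Nothing in the article separates the rating of mRS, INPHGS and MMSE, which can be blinded, from the handling of operative, shunt and imaging information, which cannot.

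**Working it through.** The point rests on no figure, so the check sets the sections side by side, by role and then by outcome.

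**Roles**

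| Role | Claimed (3.7) | Tasks stated | Can the claim hold? |
|---|---|---|---|
| Data collectors | Blinded | Baseline data, perioperative conditions, shunting outcomes, scales, Evans index, complications, serious adverse events (3.14) | No, once surgery has taken place |
| Assessors | Blinded | Evaluate each participant at each visit (3.11) | Yes for mRS, INPHGS and MMSE, if kept apart from operative, shunt and imaging information |
| Analysts | Blinded | Analysis | Yes, with coded groups |

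The collectors' baseline work is done at admission and raises no difficulty. The conflict begins with the perioperative record. An operation with a ventricular catheter and a cranial valve (3.9) cannot be confused with one that has an L3/4 catheter and a flank valve (3.10). The shunting outcomes and complications that the same collectors then record concern that hardware.

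**Outcomes**

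1. *Shunt failure (3.12).* Most of the listed events are faults of the shunt itself. To establish that a catheter is blocked, broken, exposed or misconnected, someone must examine it or read a report on it, and its site is the allocation. The last limb, any condition requiring revision, depends on a treatment decision made in an open-label trial.
2. *Favorable outcome (3.13).* It combines shunt success with a change in mRS. Shunt success is defined partly by the absence of revision (3.12), so this component has the same limit even if mRS is rated blind.
3. *Evans index (3.13).* It is a measure of ventricular size taken from MRI. After VPS a catheter lies in the lateral ventricle, and LPS as described places nothing inside the skull. The images needed for the measurement will therefore ordinarily show the arm. The lumbar and abdominal imaging in the Figure 1 footnote covers further regions that hold shunt tubing.
4. *mRS, INPHGS and MMSE (3.13).* None of these requires sight of the shunt, the operative notes or the images. Blinding is feasible.

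Open-label treatment and blinded assessment are compatible with each other, so 3.2 and 3.7 do not conflict on that ground. The conflict is between the blinding claim in 3.2 and 3.7 and the tasks and definitions in 3.12 to 3.14.

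**The case against.** The strongest reply is that a journal article condenses the protocol. Covered operative sites, handling of images and adjudication of events may all be set out elsewhere, and their absence here is no fault. That is right, and the point does not rest on their absence. It rests on a positive claim that the article's own task list and outcome definitions contradict. Added masking detail would not help unless the tasks were also divided differently.

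A second reply is that collectors and assessors are separate roles, and that no section gives the assessors operative notes or MRI. This stands. The documented overlap concerns the collectors only. A reader might infer from the different incisions that the assessors' scale ratings are unblinded too. The article does not say what assessors can see at a visit, so that inference is unsupported.

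A third reply is that perioperative conditions is undefined and might leave out anything that identifies the arm. That is possible, but the same collectors also record shunting outcomes and complications, so the conflict remains.

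A fourth reply is that hardware events, infection, revision and an imaging measurement leave less room for opinion than a symptom scale. This largely stands and limits the likely harm. Nor would masking an assessor remove discretion from the decision to revise. If objectivity is the real protection, the plan should rely on it openly rather than on blinding.

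Two further inferences are tempting. One is that expectation bias would favor LPS, because the Introduction says a growing number of studies prefer it. The same section also reports more revisions with LPS (7%, against 1% in a historical VPS trial), while Sample size (3.6) cites failure rates of 18.0% for VPS and 14.0% for LPS. The expectations for shunt failure run both ways. The other is to put a figure on the bias. The documents give no misclassification rate from which to compute one.

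**Conclusion.** The claim that data collectors are blinded cannot hold with the tasks assigned to them, and neither shunt failure nor Evans index can be blinded as described. The favorable outcome is affected through shunt success. The analysts, and the assessors' rating of mRS, INPHGS and MMSE, are not affected and can be blinded.

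A reader might go further and say that the primary outcome and Evans index are in fact assessed unblinded. The article does not say who judges failure or who reads the images, so the supportable statement is that blinding is not achievable as described.

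The size and direction of any bias are unknown. The conclusion assumes only that the perioperative and shunt records carry ordinary content, and that a ventricular catheter is ordinarily visible on the brain images used for Evans index. This should be corrected because it concerns the primary outcome and the remedy is cheap. It does not show that the comparison is biased.

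**What to change.** Reconcile sections 3.2, 3.7, 3.11, 3.12, 3.13 and 3.14, using the staff already planned:

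- Keep both collectors, so that duplicate recording is preserved, for perioperative, shunt-outcome, complication and imaging data, and declare them unblinded.
- Have the two assessors alone rate mRS, INPHGS and MMSE, without access to operative notes, shunt records or imaging and with operative sites covered at visits.
- Base shunt failure on documented, dated events.
- Describe the trial as open-label with blinded assessment of the clinical scales and blinded analysts, and claim no blinding for shunt failure or Evans index.

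One check goes with this. Data monitoring (3.16) places assessors and data analysts on the committee that checks the data yearly. The article does not say whether these are the same people as the outcome assessors and trial analysts. If they are, the separation above would need to cover that work too.

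The cost is a weaker blinding claim, a minor reassignment of roles, and covering operative sites at visits. Treatment, sample size and visit schedule do not change.
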